### 2.12. Blinding

Blinding is impossible in the present intervention, due to its educational nature. However, to reserve a certain level of blinding, to maintain and protect the bias sources, some measures have been taken. Detailed information related to blinding is shown in Table 3.

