### 2.2. Study Design

This is a two-arm, single-blind, individual, randomized, controlled trial that will determine the effectiveness of pharmacist-led educational interventions for the patients who approached pharmacies with LRTI prescriptions. The present study will be conducted in a community-pharmacy setting in the rural region of Pakistan. The iRCT will be favored to reduce possible contamination between the two groups. The standard protocol items; recommendation for interventional trials (SPIRIT) used in the current trials are presented in Figure 1 and the checklist (Additional File S1).

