### 2.10. Concealment of Allocation

Before preceding to random allocation into either the control or intervention arm of the study, an informed consent/agreement ascertainment and eligibility will be obtained. The allocation will not be known to research assistants, participants, or trial representatives (pharmacists) until the point of randomization. Interventional households will only be known to research assistants. The participants will be introduced to the interventional arm facilitator individually, by mobile phone call. If the pharmacists and research teams are allocated to the control arm, they will continue to regularly contact the allocated UC.

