### 2.16. Trial Data Management

Data will be managed per established norms. Monitoring will be required at all stages to gather true, authentic, and verified data. Every day, the principal investigator’s field office will save the data on a paper evaluation study booklet with a participant’s given codes. The data will be checked by the lead investigator, with all highlighted queries being rectified as soon as possible, and any discrepancies being resolved by a third data entry person. Following the creation of electronic files, all data will be password-protected, and only authorized individuals will have access to the database, which will be backed up every day. The participant’s information will remain confidential to maintain quality and data secrecy. Only pharmacists will be aware of the private information in the intervention; all data forms will be kept in closed filing cabinets. The trial team will monitor the trial progress on a daily basis.

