### 2.17. Statistical Analysis Methods

According to the Consolidated Standards of Reporting Trials (CONSORT) for RCTs, all the findings will be reported as per the given guidelines [41]. Data will be analyzed through IBM-SPSS-Statistics (version 21) and STATA (version 11). The basis of primary analysis is to educate the population with LRTIs, and the secondary analysis will be based on the adherence rate and behavior of the population. For the primary endpoint analysis, a linear mixed model will be employed. The mixed model will include the visits, interactions with the treatment group, and baseline measurement of BMQ and PAS-QA as covariates, and subjects as a random effect. The mean differences (MD) between the two arms at each visit, with a confidence interval (CI 95%), will be derived from a generalized mixed model, along with each visit from the treatment arm. Before unmasking the trial, all analyses will be defined in detail with their assigned statistical plans.

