**INTERVENTIONS:**									
leaflets									
Booklets									
WHO awareness									
Usual Care									
**ASSESSMENT:**									**Outcomes analysis**
Baseline variables	x	x	x	x	x	x	x	x	
Therapy success rate	x	x	x	x	x	x	x	x	
Primary Outcomes									
Overall Adherence Secondary Outcomes	x	x	x	x	x	x	x	x	

**Table 3 antibiotics-10-01147-t003:** Overall trial blinding strategies.

Stakeholders	Allocation	Pharmacist-Led Interventions	Community Pharmacists	Outcome Assessment	Data Analysis
Trial Observer (PI)	a	a	a	a	a
Trial Participants	n/a	n/a	n/a	n/a	n/a
Duty Pharmacists	n/a	a	a	n/a	n/a
Data accumulators	n/a	n/a	n/a	n/a	n/a
Data analysts	n/a	n/a	n/a	n/a	a

a: aware; n/a: not aware. PI: principal investigator.

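### The trial is labelled single-blind without naming a blinded party, and Table 3 lists participants as unaware of an education they receive in person and report on themselves

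*Protocol article*

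**What the plan says.** Section 2.2 opens: "This is a two-arm, single-blind, individual, randomized, controlled trial". The blinded party is not named there or elsewhere.

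Section 2.12 says: "Blinding is impossible in the present intervention, due to its educational nature". The next sentence softens this: "However, to reserve a certain level of blinding, to maintain and protect the bias sources, some measures have been taken". For the detail it points to Table 3.

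Table 3 crosses five stakeholders with five columns (Allocation, Pharmacist-Led Interventions, Community Pharmacists, Outcome Assessment, Data Analysis). Its key reads "a: aware; n/a: not aware". The columns are not otherwise defined.

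Three other sections bear on masking:

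- Section 2.10, on who knows the intervention arm: "Interventional households will only be known to research assistants".
- Section 2.16, on data cleaning: "The data will be checked by the lead investigator, with all highlighted queries being rectified as soon as possible".
- Section 2.17, on analysis: "Before unmasking the trial, all analyses will be defined in detail with their assigned statistical plans".

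**The concern.** The primary outcomes in section 2.14.1 (BMQ and PAS-QA) are questionnaires on beliefs and knowledge, and the MMAS-8 in section 2.14.2 is self-reported adherence. Intervention participants are taught what good antibiotic use looks like and are then asked about it. Such outcomes are open to desirability in the respondent and to expectation in whoever asks, queries or analyses.

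An educational intervention leaves little scope for masking participants. Masked assessment, data cleaning and analysis are then the main protections left, and on these the document is inconsistent or unclear. If the trial is reported as single-blind with participants unaware, readers will credit it with a safeguard it does not have.

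**Working it through.** No arithmetic formula applies. The check is a reading of Table 3 cell by cell against the text.

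**Cells marked not aware, by row**

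| Stakeholder | Not aware | Aware |
|---|---|---|
| Principal investigator | 0 of 5 | all columns |
| Participants | 5 of 5 | none |
| Duty pharmacists | 3 of 5 | Pharmacist-Led Interventions, Community Pharmacists |
| Data accumulators | 5 of 5 | none |
| Data analysts | 4 of 5 | Data Analysis only |

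In the Allocation column, 4 of 5 stakeholders are not aware. Only the principal investigator is aware.

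**Row by row against the text**

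1. *Participants.* Section 2.10 hides allocation from them only up to randomisation, then has participants introduced by phone to the facilitator of the intervention arm. Intervention participants get a leaflet (2.5.1), a booklet and oral counselling (2.11) and educational calls (2.5.2). The row makes no distinction by arm, so it declares these people unaware of the intervention given to them. That cannot be right, and it conflicts with section 2.12.

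2. *Duty pharmacists.* Table 3 has them unaware under Allocation. Section 2.9 has coordinators tell individual pharmacists the allocation once the participant has agreed to take part. The two agree only if the column means concealment before randomisation, which the table does not say.

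3. *Principal investigator.* Aware in every column, including Outcome Assessment and Data Analysis. Read literally, this also conflicts with the sentence in section 2.10 that limits knowledge of intervention households to research assistants. Sections 2.11 and 2.16 have the lead investigator collect the data weekly and check them. If the lead investigator is the principal investigator, which the document suggests but does not state, data queries are raised by someone who knows the arm.

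4. *Data accumulators.* Unaware throughout, including Outcome Assessment. Section 2.4, however, forms the data-collector team from pharmacists, LHWs and vaccinators, and requires pharmacists and other healthcare members to be trained for counselling. Section 2.13 has pharmacists contact intervention participants before follow-up, with a survey completed by call where possible. No section says that the person who assesses differs from the person who counselled.

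5. *Data analysts.* Unaware under Allocation, aware under Data Analysis. That second entry could mean that they know the arms when analysing, or merely that they know the analysis. The reference to unmasking in section 2.17 suggests some masking beforehand, but does not say of whom.

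Section 2.11 also says that the pharmacist team stays blinded to outcomes. That is not blinding to allocation, so it does not supply the missing party.

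**The case against.** The strongest reply is that section 2.12 does not claim full blinding. It concedes the limit and offers partial measures, and Table 3 does list masked parties: data accumulators in every column, analysts in four of five. Section 2.17 fits with masking up to the analysis. This stands. A reader might infer from the contradiction that nobody who could be blinded is blinded, or that the analysts are unblinded. The document supports neither: the accumulators' row says the opposite, and the analysts' single aware entry is ambiguous.

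A reader might also infer that the staff who deliver the education are the ones who score it. Section 2.4 shows overlapping types of staff, not the same individuals, and no section says who administers the questionnaires or counts the pills. Section 2.5.2 places the first adherence call before the later educational calls and makes week 7 the assessment week, so assessment and education calls are largely separate as written. What can be said is that separation of roles is not stated.

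It could be argued that participants are unaware in the sense of not knowing that theirs is the experimental condition, since section 2.6 gives both arms routine calls. No such measure is described, and the introduction to the intervention-arm facilitator in section 2.10 works against it.

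Finally, one might want a figure for the bias. Any percentage shift across the adherence cut-off would be invented. Adherence is also listed as secondary in section 2.14.2, so such a figure would not speak to the primary questionnaires.

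**Conclusion.** The point holds as a contradiction between the stated design and its description. The single-blind label has no named and credible blinded party; the participant row of Table 3 cannot be true as written; and the masking of those who assess, query and analyse is not coherently stated. The principal investigator's awareness at outcome assessment and analysis is explicit. The duty-pharmacist entry is a conflict only if the Allocation column covers the time after randomisation.

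The size of any bias cannot be derived from the document. On these outcomes, knowledge of the arm could plausibly favour the intervention, but that is a judgement, not a computed effect. The conclusion rests on reading Table 3 by its own key. If some of its entries were meant as not applicable, the table still needs correcting.

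**What to change.** 1. In section 2.2, replace the label with a description: open to participants and delivering pharmacists, with masked outcome assessment and analysis. Bring sections 2.10 and 2.12 into line.
2. In Table 3, mark participants and duty pharmacists as aware, and define the columns, in particular whether Allocation means before or after randomisation.
3. State that analysts work with arms coded A and B until the primary model has been run. This also gives the unmasking in section 2.17 a definite meaning.
4. Mark the principal investigator as not aware at outcome assessment and analysis, and raise data queries on forms that do not show the arm.
5. Have the week-2 and week-7 questionnaires and the pill count done by existing data collectors who did not counsel that participant. Assign this by participant rather than by profession, because section 2.4 trains several professions to counsel.

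The cost is a rota change within the existing team, coded data sets and a corrected table; no additional participants are needed. An assessor who did not counsel may still learn the arm from the participant or, under section 2.10, as a research assistant, so the rota should exclude those who hold the arm list. None of this removes the participants' own desirability bias, which should be stated as a limitation.

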### 2.13. Participant Timeline

To control the attrition rate among patients, pharmacists will contact all intervention study participants that were enlisted via phone or text message before their scheduled follow-up session. LRTI patients who have some issues or are not prepared for a follow-up visit will be revealed, and the self-actualization survey will be completed via call if possible. The appointment can be moved to an alternate day, but the one-week treatment outcomes must be reported through mobile phone. The outcomes of the study will be based on measures of primary and secondary outcomes.

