#### 2.5.2. Telephone-Based Follow-Up

After the educational interventions at the community pharmacies, a follow-up will be continued up until the 7th week. The first telephone call will be made at the start of the second week and the therapy success will measure the rate of adherence to the prescribed antibiotics. Then, a follow-up with a brief educational strategy will continue throughout the study period, and a 3rd, 4th, 5th, and 6th call will be made to enhance the participants’ knowledge related to proper antibiotics use. The 7th week of the trial will be the assessment week and will measure the overall knowledge as a primary and secondary outcome.

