### 2.6. Boost Usual Care (BUC)

Participants in the intervention and control (arms) groups will continue to receive pre-planned, routine telephone calls on an individual basis and the care would be considered enhancement care. The primary care, the antibiotics therapy, will not involve any placebo, and the focus will adhere to the prescribed treatment. The usual care will consist of: (i) primary healthcare provider, pharmacists and assistants trained in interaction with and supervision of treatments with antibiotics; (ii) providing feedback results to all participants about their assessment; (iii) information will be provided about the options for appropriate care and treatment through the nearest tehsil headquarter hospital (THQ) or tertiary care facility.

Both arms are equally free to BUC through their routine health providers. Finally, on the 7th week, the strength of the services will be measured. The evaluation will be carried out and reported in a timely manner.

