### 2.7. Sample Size

The previous literature will serve as a guide for calculating sample size, based on the effect of the prescribed antibiotics and pharmacist-led educational interventions on successful adherence to therapy [31,32]. A sample size of the responses will be required to give a 95% confidence interval with a 5% margin of error. Therefore, the maximum number patients from each pharmacy will be recruited until the study sample size surpasses both groups (control and interventions). Once the sample size is achieved, the principal investigator and team members will halt the patient recruitment. We will aim to achieve a 1:1 allocation ratio in the intervention or control groups, with 80%’ power and an alpha error of 5%. For the dropout participants, a 20% attrition rate will be supposed, resulting in a minimum sample size of 400 (200 in each group).

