### 2.11. Data Collection

At first, data from patients’ medical records reporting LRTIs (medical notes will be checked for the diagnosis) would be collected by trained pharmacists at community pharmacies, and the pharmacist team will remain blinded to the outcomes. A complete booklet of educational written information will be provided to participants in each interventional arm. The booklet will include materials that are relevant to antibiotic use, such as graphical leaflets, antibiotic dosing regimens kept on sticky notes, adherence, and prevention of antibiotic storage in the home. Following this textual counseling, oral/verbal counseling will be delivered in the patient’s usual area of counseling at a pharmacy. The patient’s information will be transferred to pre-determined data collection forms and stored securely. For the follow-up phase, patients’ valid mobile phone numbers will be collected and retained for future contact and follow-up. The trial team members will contact the participants through their mobile phones in both union councils. After one week, patients will be asked to exhibit their prescribed antibiotics, and the first therapy outcomes will be checked at the beginning of the second week. Finally, in the final session of the trial, a qualitative interview will be scheduled for the 7th week of the study. To keep data quality high, data collection should be current and dependable. As a result, at least three meetings will be held for the field assistance members (pharmacists) to keep the records up to date. The lead investigator will collect all data once a week, as in Table 2.

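### The pre-follow-up reminder meant to control attrition is specified for intervention participants, with no equivalent written for controls

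*Protocol article*

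**What the plan says.** Section 2.13 (Participant Timeline) says: "To control the attrition rate among patients, pharmacists will contact all intervention study participants that were enlisted via phone or text message". The contact is to come ahead of the follow-up visit. The section goes on to provide for completing a survey by call and for moving an appointment. Those later sentences speak of LRTI patients and of the appointment, and name no arm.

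Other sections deal with telephone contact, but not with a reminder before follow-up:

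- Section 2.6 (Boost Usual Care): "Participants in the intervention and control (arms) groups will continue to receive pre-planned, routine telephone calls on an individual basis".
- Section 2.11 (Data Collection): patients' "valid mobile phone numbers will be collected and retained for future contact and follow-up", and "The trial team members will contact the participants through their mobile phones in both union councils".
- Section 2.10 (Concealment of Allocation): staff allocated to the control arm keep up regular contact with their union council.
- Section 2.5.2 (Telephone-Based Follow-Up), under the intervention group: "a follow-up with a brief educational strategy will continue throughout the study period, and a 3rd, 4th, 5th, and 6th call will be made".

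For the sample size, section 2.7 says that "a 20% attrition rate will be supposed", which leads to 400 patients, 200 per group. It is one rate, not given by arm.

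**The concern.** Every outcome in this trial needs the patient to stay in touch. The BMQ, PAS-QA and MMAS-8 are questionnaires, and a pill count needs the patient to show or report what is left. Patients who are easy to keep in contact are plausibly also those who take their antibiotics as prescribed, so who is lost may be related to the outcome.

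If one arm is reminded before each follow-up and the other is not, loss may be lower in the reminded arm and the completers in the two arms are no longer alike. The comparison then mixes the effect of the education with the effect of the reminder on who is measured. There is a secondary effect on mode of collection. The reminder is how patients who cannot attend are identified, so a one-sided reminder could also make telephone completion and rescheduling more common in one arm, although the text does not restrict them.

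**Working it through.** **1. Passages side by side.** Section 2.13 is the only place where contact is tied to attrition, and it names intervention participants. Sections 2.6, 2.10 and 2.11 establish that controls are contacted. Their stated purposes are enhanced usual care, continued contact with the union council, and data collection; none mentions a reminder before follow-up. Section 2.7 plans for equal loss. The sections are not reconciled on this one step.

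**2. The plan's own figure.** 400 × (1 − 0.20) = 320 evaluable, or 160 per arm. Section 2.7 gives no effect size, SD or rates, so 400 cannot be reproduced from a power calculation. The point here does not depend on it.

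**3. Does unequal loss cost power?** Hardly. Assume a two-sided 5% test. With 160 per arm, 80% power corresponds to (1.960 + 0.842) × √(2/160) = 0.313 SD. Holding that effect and 20% total loss fixed:

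| Loss, intervention / control (assumed) | Analysed | Power |
|---|---|---|
| 20% / 20% | 160 / 160 | 80.0% |
| 15% / 25% | 170 / 150 | 79.8% |
| 10% / 30% | 180 / 140 | 79.4% |

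**4. Does it cause bias?** Let *p* be true adherence (the same in both arms, so no effect), *q* adherence among those lost, and *d* the loss in an arm.

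Completer adherence = (p − d·q)/(1 − d) = p + (p − q)·d/(1 − d)

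The spurious difference, intervention minus control, is therefore (p − q) × [d_I/(1 − d_I) − d_C/(1 − d_C)].

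- 15%/25%: 0.15/0.85 − 0.25/0.75 = 0.1765 − 0.3333 = −0.1569
- 10%/30%: 0.10/0.90 − 0.30/0.70 = 0.1111 − 0.4286 = −0.3175

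| p = 50%; assumed q | 20%/20% | 15%/25% | 10%/30% |
|---|---|---|---|
| 40% | 0 | −1.6 points | −3.2 points |
| 30% | 0 | −3.1 points | −6.3 points |
| 20% | 0 | −4.7 points | −9.5 points |

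Only the gap p − q matters: p = 60% with q = 30% gives the same −4.7 and −9.5 as the last row. In these scenarios the bias runs against the intervention, because more poor adherers are kept in that arm. If those lost were the better adherers, the sign would reverse.

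**5. On a continuous score.** If those lost lie 0.25 to 0.5 SD below the overall mean, the same bracket gives −0.04 to −0.08 SD at 15%/25% and −0.08 to −0.16 SD at 10%/30%, for a simple comparison of completers. This is not an estimate of bias in the mixed model.

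All loss splits and all values of *p* and *q* are assumptions; the article gives none.

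**The case against.** The strongest reply is that the sentence is loosely worded and nothing more. Section 2.13 does not say that controls get no reminder. Its stated aim concerns patients in general, and its phrase can be read as everyone enlisted in an intervention study. Phone numbers are collected without regard to arm, and both arms are called. This stands to the extent that exclusion of controls is not established. It does not remove the point. Section 2.6 names both arms when both are meant, the abstract uses the word study as the label of the intervention arm, and a field team could reasonably apply section 2.13 to one arm.

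A reader might also infer that the reminder is an unplanned co-intervention. The article does not support that. Sections 2.5 and 2.5.2 make telephone contact a declared part of the intervention, and section 2.6 plans calls in both arms. The reminder is an extra contact not listed as intervention content, and its own effect could not be told apart from the rest of the telephone package.

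Two further objections carry weight:

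- The loss splits are invented, and a reminder might change loss little when both arms are already telephoned. They show what could happen and are not a forecast.
- The illustration uses completer adherence, which section 2.14.2 makes a secondary outcome (section 2.1 makes it the main objective). The primary outcomes, BMQ and PAS-QA, go into a mixed model with visits and baseline scores (section 2.17). That model can deal with loss explained by observed data, and further handling of missing data may be in an analysis plan that is not shown. What remains is loss that depends on unobserved adherence or beliefs, which the model cannot be relied on to correct.

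**Conclusion.** The point holds as a defect of wording with a possible cost in bias. Read as written, section 2.13 gives retention effort to one arm, and no other section supplies the same step for controls, while section 2.7 assumes equal loss. The cost would be bias; the loss of power is negligible (80.0% to 79.4% at worst in the scenarios tabulated). Its size and direction are unknown: −1.6 to −9.5 points in completer adherence under the assumed splits and gaps, zero if loss is equal and those lost differ from completers equally in both arms, and of opposite sign if better adherers are the ones lost.

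A reader might be tempted to set these figures against a target difference of about 15 points. The article states no such target. A back-calculation from 160 per arm gives about 13 to 16 points, but only by assuming control rates of 30% to 70%. Nor does the article show that differential follow-up will occur, only that the text permits it. The change is worth making because it is cheap and is needed on either reading of the sentence.

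**What to change.** Reconcile section 2.13 with sections 2.6 and 2.11 by replacing the contact sentence with, for example: *All participants in both arms will receive the same phone or text reminder before each scheduled follow-up, with the same option to reschedule and to complete the survey by telephone, on the same schedule. The reminder will carry no educational content.*

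If the present wording was already meant to cover the whole trial, this only makes it explicit. Loss by arm will appear through the CONSORT reporting to which section 2.17 commits, so no separate provision is needed.

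The cost is one sentence, plus reminder texts or calls to about 200 control patients who are already being telephoned under section 2.6. The sample size and the analysis do not change.
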